## Abstract

**Background:**

Ageing populations and the increasing prevalence of chronic diseases pose major challenges to health care systems in high-income countries, especially in rural areas affected by a decline in public services. This trial investigates a new short-stay hospital model, STATAMED, which adopts a general medical approach to addressing the needs of adult patients (18 years or older) with chronic diseases and/or acute infections, with a particular focus on the elderly. STATAMED short-stay wards will incorporate a mandatory case review between the referring physician and the lead STATAMED physician, as well as support from case managers and mobile nurses to ensure coordination and continuity of care after hospital discharge. The primary aim of the trial is to determine whether the care provided in STATAMED wards is more effective than usual hospital care in improving the combined primary outcome of hospital length of stay and 30-day hospital readmission rates.

**Methods:**

The study will be conducted as a prospective, cluster-randomised controlled trial using a stepped-wedge design. STATAMED wards will be implemented at six hospital sites, and the catchment areas will be divided into clusters. All referring entities in a catchment area—including general practitioners (GPs), office-based specialists, nursing homes, ambulatory care services, and emergency services—will be potential candidates for cluster formation. The intervention group is expected to consist of 4481 patients. Primary and secondary outcomes will be assessed using claims data from participating statutory health insurers. A health economic evaluation will also be conducted using these data to compare costs associated with STATAMED and usual care. To minimise the risk of bias, analyses will be conducted on both an intention-to-treat and actual treatment basis.

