### Sample size {14}

The required sample size was estimated prior to project implementation using Bonferroni correction to account for multiple comparisons because the trial includes two co-primary outcomes without a hierarchical structure: (1) length of hospital stay and (2) 30-day hospital readmission. Applying a type 1 error rate of *α* = 5%, the Bonferroni correction results in a per-outcome significance level of α/2 = 2.5% for confirmatory testing.

Sample size calculations were performed according to Woertman et al. [38]. Based on existing literature [39] and a pre-analysis of claims data, a minimum relevant difference of 15% was specified for both co-primary outcomes. An intra-class correlation coefficient (ICC) of *ρ* = 0.05 was assumed to account for within-cluster correlation [40, 41], resulting in a design effect estimate of 0.61.

For co-primary outcome (1), the required sample size was estimated at 2331 participants; this increases to 2681 participants after adjusting for a 20% drop-out rate. For co-primary outcome (2), the required sample size was estimated at 3724 participants, rising to 4481 after applying the same drop-out assumption. Given that both outcomes are co-primary, the larger of the two estimates (i.e. 4481 participants) was initially adopted as the required sample size for the intervention group across all clusters over the full duration of the study.

These initial calculations relied on conservative assumptions, including a high estimated drop-out rate and the use of the Bonferroni correction for multiple comparisons. However, evidence from the literature and ongoing implementation experience allow for the following refinement of these assumptions.

Based on recent experience with implementation logistics and recruitment patterns, a more realistic drop-out rate of 15% is now assumed. In addition, Leppin et al. [42] conducted a meta-analysis that found an 18% reduction in the risk of readmission. Complex interventions and interventions ensuring structured follow-up care are found to be particularly effective in reducing readmission. Because both elements are core features of STATAMED, an effect size of 20% is considered plausible.

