Finally, to adjust for multiple comparisons, the Romano-Wolf method [43] offers an alternative to the Bonferroni correction. This method controls the family-wise error rate using a step-down bootstrap procedure that accounts for the correlation among hypotheses, thereby making more efficient use of the global *α* level. Applying this method permits the use of a global significance level of 5% for sample size calculation.

Under these updated assumptions (i.e. 20% effect size, 15% drop-out rate and Romano-Wolf correction), the required sample size is reduced to 2076 participants for the readmission outcomes and 578 for length of stay. Accordingly, 2076 participants are required for evaluating the combined primary outcome.

The sample size calculation refers to the required number of participants for whom claims data are available. This is important because claims data are only available for patients insured by one of the participating statutory health insurers.

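### The abstract gives an expected intervention group of 4481, the initial requirement that the sample-size section of the same version has reduced to 2076

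*Protocol article*

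**What the plan says.** The Methods paragraph of the abstract states without qualification: "The intervention group is expected to consist of 4481 patients".

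Sample size {14} gives that number a history. Initially, "a minimum relevant difference of 15% was specified for both co-primary outcomes", and "the Bonferroni correction results in a per-outcome significance level of α/2 = 2.5% for confirmatory testing". For readmission, "For co-primary outcome (2), the required sample size was estimated at 3724 participants", "rising to 4481 after applying the same drop-out assumption", that assumption being 20%. The section then says that "the larger of the two estimates (i.e. 4481 participants) was initially adopted as the required sample size for the intervention group".

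The same section goes on to call these assumptions conservative and changes three of them: drop-out to 15%, effect size to 20%, and the multiplicity method to Romano-Wolf at a global 5%. With these, "the required sample size is reduced to 2076 participants for the readmission outcomes and 578 for length of stay". It concludes that 2076 is the number needed for the combined primary outcome, and that the calculation counts participants with available claims data.

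Statistical methods for primary and secondary outcomes {20a} says a Bonferroni correction will be applied, at a one-sided 2.5% for each primary outcome, and that Romano-Wolf may be used as an alternative.

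**The concern.** The abstract and the sample-size section give different numbers for the size of the intervention group, and the abstract's is the one the section has set aside. This is not a difference between an amendment log and current text: Trial status describes a single version, dated 17 July 2025, and both figures belong to it.

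A reader who takes the size from the abstract will think of a trial sized to detect a 15% reduction, the minimum relevant difference, at 2.5% per outcome. The requirement now stated is sized for a 20% reduction at 5% and is less than half as large. Readmission is the outcome that sets both numbers, and the Objectives section uses it to check that shorter stays do not compromise quality. The document should therefore be clear about what size of readmission effect it is planned to detect.

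**Working it through.** **Inputs.** All from Sample size {14}. Initial: 3724 before drop-out and 4481 after, 15% difference, 2.5% per outcome, 20% drop-out. Current: 2076 after drop-out, 20% effect, 5% level, 15% drop-out. Power and the baseline readmission rate are not printed, and {14} does not state sidedness ({20a} says one-sided). I therefore assume 80% or 90% power and show one- and two-sided tests. The scaling treats the standardised effect as proportional to the relative reduction, an approximation forced by the missing baseline rate.

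**1. Origin of 4481.** 3724 × 1.20 = 4469, which is 0.3% below 4481. 3724 / 0.80 = 4655, which is 3.9% above. So 4481 is the initial readmission requirement, with drop-out applied as N × (1 + d), apart from a small rounding difference. The abstract's figure matches it to the digit.

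**2. Is 2076 a recalculation that replaces it?** Net N = 3724 × (15/20)² × [(z_new + z_power) / (z_old + z_power)]², where z_old is at 2.5% and z_new at 5%. The net figure is then inflated for 15% drop-out in both common forms (results from unrounded values).

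| Assumed power | Test | Alpha ratio | Net N | × 1.15 | / 0.85 |
|---|---|---|---|---|---|
| 80% | one-sided | 0.788 | 1650 | 1898 | 1941 |
| 80% | two-sided | 0.826 | 1730 | 1989 | 2035 |
| 90% | one-sided | 0.815 | 1707 | 1963 | 2009 |
| 90% | two-sided | 0.847 | 1773 | 2039 | 2086 |

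The range is 1898 to 2086. The two-sided / 0.85 cases, 2035 and 2086, lie within 2% of 2076. So 2076 follows from the three stated changes and replaces 4481 as the requirement.

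**3. Ratio.** 2076 / 4481 = 0.46.

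**4. Readmission power of 2076 under the initial assumptions (15% difference, 2.5%).** With m evaluable participants, ncp = (z_old + z_power) × √(m / 3724) and power = Φ(ncp − z_old). Example, two-sided, 80%: m = 2076 / 1.20 = 1730; ncp = (2.241 + 0.842) × √(1730 / 3724) = 2.10; power = Φ(2.101 − 2.241) = 0.444.

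| 4481 sized for | Test | m = 1730 (2076 / 1.20) | m = 1765 (2076 × 0.85) | m = 1805 (2076 / 1.15) |
|---|---|---|---|---|
| 80% | two-sided | 0.444 | 0.453 | 0.462 |
| 80% | one-sided | 0.480 | 0.487 | 0.496 |
| 90% | two-sided | 0.563 | 0.573 | 0.584 |
| 90% | one-sided | 0.598 | 0.607 | 0.617 |

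This gives 44–50% or 56–62%. Taking 20% drop-out as 2076 × 0.80 = 1661, a form that 4481 does not match, would lower the bottom ends to 43% and 54%.

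**5. Readmission power of 2076 under its own assumptions (20% effect, 5%, 15% drop-out).** Multiplying ncp by 20/15 and using z_new gives 81–83% if 4481 was sized for 80%, and 90–91% if for 90%.

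**6. If Bonferroni is kept with the other two changes.** Alpha does not change, so the z-terms cancel: 3724 × (15/20)² = 2095. With drop-out, 2095 × 1.15 = 2409 or 2095 / 0.85 = 2465. At 2.5% and a 20% effect, 2076 itself would have 72–74% power (80% sizing) or 84–85% (90% sizing).

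**The case against.** The strongest reply is that the two numbers measure different things. The abstract speaks of what is expected; {14} speaks of what is required, and only among participants with claims data. Table 1 and the Discussion refer to participants outside the participating insurers, so enrolment could exceed the claims-data minimum. An expectation above a minimum is not a logical contradiction. That reading is possible but unsupported: the Trial design section requires eligible individuals to be covered by a participating insurer, no section forecasts recruitment of 4481, and the figure is exactly the initial requirement. An abstract that was not updated is the likelier explanation.

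It is also fair that {14} openly gives both numbers and the three changed assumptions. Someone who reads that section is not misled, and no analysis or decision rule depends on the abstract sentence. This stands, and it limits the weight of the point.

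Three stronger readings are tempting, and the documents do not support them:

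- **That the trial's power has roughly halved, to about 44–45%.** Each size was presumably set to the same nominal power under its own assumptions, and step 5 is consistent with that. The low figure applies a 15% effect and a 2.5% level to a size calculated for 20% and 5%, and it is only the two-sided, 80% corner of the range.
- **That the funder would over-read a null readmission result.** Interpretation will rest on the achieved sample and its confidence interval, so this is speculation.
- **That 4481 is an arithmetic error.** It reproduces to within 0.3% from the initial inputs. The fault is consistency between sections.

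**Conclusion.** The point holds as an inconsistency between the abstract and the body of one version. The abstract's 4481 is the initial requirement, 2076 is the current one (46% of it), and the document neither reconciles them nor supports 4481 as a forecast.

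The practical difference lies in the effect each size is planned to detect. Held to the initial 15% difference at 2.5%, 2076 would give about 44–50% readmission power if 4481 was sized for 80%, or 56–62% if sized for 90%. These ranges rest on assumed power, both sidedness options, the drop-out forms tabulated above and the proportional-effect approximation.

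Copying 2076 into the abstract would not be enough. That number depends on testing at 5% under Romano-Wolf, while {20a} commits to Bonferroni and leaves Romano-Wolf optional. The governing size is not settled until those two sections agree.

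**What to change.** State one governing size in the abstract and in Sample size {14}, with its effect size, alpha, drop-out and power. The route depends on the confirmatory method:

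- **Romano-Wolf is confirmatory:** say so in {20a}, and replace 4481 in the abstract with 2076 participants with claims data, noting the reduction from 4481.
- **Bonferroni stays, as {20a} now says:** restate the requirement in {14} at 2.5% per outcome and use that figure in the abstract. By step 6 it would be roughly 2410 to 2465 for a 20% effect and 15% drop-out; the trial team should recompute it from its own inputs.
- **4481 is still the recruitment expectation:** label it as such in both places, beside the requirement, and give the power at that number.

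The cost is a sentence in the abstract, one in {14} and, on the first route, one in {20a}, plus a short recalculation if Bonferroni stays. Reconciling the text needs no change to the trial design or data collection.

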**Discussion:**

This trial will assess whether STATAMED improves health care utilisation outcomes that reflect the efficiency and quality of inpatient care and discharge planning compared to usual hospital care. The findings will provide novel evidence about how best to improve health care for patients with chronic diseases and/or acute infections and may offer evidence for cost-effective strategies to improve health care delivery.

**Trial registration:**

German Clinical Trials Register DRKS00033096. Registered on 27 November 2023, last updated on 26 May 2025.

**Supplementary Information:**

The online version contains supplementary material available at 10.1186/s13063-025-09072-6.

## Administrative information

Note: The numbers in curly brackets in this protocol refer to SPIRIT checklist item numbers. The order of the items has been modified to group similar items (see http://www.equator-network.org/reporting-guidelines/spirit-2013-statement-defining-standard-protocol-items-for-clinical-trials/).

## Introduction

### Background and rationale {6a}

Ageing populations and the increasing prevalence of chronic diseases, especially in high-income countries, pose major challenges to health care systems [1, 2]. These trends not only increase demand for health care services but also require a shift in the type of care provided. Many health systems remain overly focused on acute care, which often involves surgery or advanced diagnostic technologies rather than addressing the long-term needs of chronically ill patients [3]. Another challenge exacerbating these problems is the growing difficulty of providing adequate care in rural areas. Increasing urbanisation has led to a decline in infrastructure, public services, and cultural activities in many rural regions. This trend has also affected the availability of health care services [4–6], disproportionately impacting the remaining population, especially the elderly [7, 8].

A further problem facing many health systems is the overutilisation of medical services [9–11], which “occurs when a health service is provided under circumstances in which its potential for harm exceeds the potential benefit” [12]. The potential consequences of overutilisation include rising health care costs, inefficient resource utilisation, unnecessary stress for patients, and negative health effects [11]. Overutilisation can result from various factors, including financial incentives from remuneration systems, physician uncertainty, and patient demand. A further important cause of overutilisation is a lack of coordination among different providers of care [13, 14], particularly in countries with fragmented health care systems, such as Germany [15], where this trial is taking place. The elderly and chronically ill are especially vulnerable to the effects of fragmented care because their treatment generally requires a higher degree of coordination [16, 17].

The current trial evaluates a new model of care, referred to as STATAMED, which aims to address the challenges outlined above. At participating hospitals, a general medicine short-stay ward (“STATAMED ward”) with approximately 20 beds will be integrated into the existing hospital infrastructure. Two implementation models can be distinguished: (1) Hospitals in which a STATAMED ward is established and operates alongside existing wards and (2) hospitals in which the STATAMED ward constitutes the sole inpatient ward. In addition to standard general medical treatment, STATAMED wards will include interdisciplinary treatment planning before hospital admission (facilitated through a mandatory case review between the referring physician and the lead STATAMED physician), as well as support from case managers and mobile nurses during and after the hospital stay to ensure coordination and continuity of care after hospital discharge.

The mandatory case review between the referring outpatient physician and the lead STATAMED physician is conducted to determine patient eligibility for the trial and to collaboratively plan the treatment. While the literature supports the benefits of better-integrated models of service delivery [18], mandatory case reviews between referring physicians and lead physicians at receiving hospitals are currently neither widely implemented nor thoroughly studied.

Short-stay units are employed in various medical contexts, including paediatric care, surgical care, emergency care, and general medicine. Depending on the setting, the intended length of stay in short-stay units is typically 5 days or fewer [19]. In a meta-analysis, Damiani et al. [19] found that short-stay units reduced length of stay without adversely affecting mortality and readmission rates. However, a literature review by Strøm et al. [20] focusing on general medical conditions concluded that current evidence regarding reduced mortality, serious adverse events, and rehospitalisation is insufficient to definitively assess the benefits and harms of short-stay units.

The primary motivation for deploying case managers is to improve care coordination, which involves communication with various health care providers, social service providers, and the patients’ relatives. A literature review by Joo et al. [21] found that case managers reduce readmissions, hospital visits, emergency department visits, and length of stay.

Mobile nurses are introduced to ensure proper follow-up care after hospital discharge. Kwok et al. [22] analysed the effectiveness of mobile nurses for older patients with chronic heart failure, reporting positive effects on patient independence and indications of reduced readmissions, although no evidence of cost-effectiveness was found. Chow et al. [23] examined mobile nurse services covering various chronic diseases and identified positive effects on self-reported health status but no impact on readmission rates.

Conducting this trial is important to assess whether STATAMED contributes to improvements in care. Evaluating innovative care models is critical for determining which new approaches should be adopted as part of routine care. This is particularly important given the budget constraints that most health care systems face and their obligation to allocate public funds effectively and efficiently. This consideration is especially relevant to the statutory health insurance system in Germany, where health expenditures per capita are among the highest in Europe, yet health outcomes are not always commensurate with this level of spending [24]. This trial is also highly relevant in light of the current challenges facing the German hospital sector. The hospital market in Germany is characterised by excess capacity in terms of hospital beds [25] and a concurrent shortage of nursing staff [26, 27]. A reform of the hospital sector is currently being planned, with the dual goal of reducing the number of hospital sites and improving the quality of care in the remaining facilities. One focus of this reform concerns the role of small hospitals, particularly those in rural areas. Proponents argue that these hospitals are vital for ensuring timely access to inpatient care, whereas critics contend that they struggle to maintain sufficient quality due to low patient volumes. In this context, STATAMED may provide a viable solution for maintaining broad access to general medical care in hospital settings while addressing inefficiencies and improving health outcomes.

## Objectives {7}

The primary aim of this study is to investigate whether STATAMED reduces the length of hospital stay and 30-day hospital readmission rates (combined primary outcome) in the target population, which comprises adult patients with chronic diseases and/or acute infections (see the “Eligibility criteria {10}”). To achieve this, the following interventions will be implemented: a mandatory case review between the referring physician and the lead STATAMED physician to determine patients’ eligibility for the trial and to collaboratively plan their treatment, standard general medical care delivered in a general medical short-stay hospital ward with approximately 20 beds, discharge planning and follow-up care coordinated by case managers, and post-discharge care delivered by mobile nurses (see the “Intervention description {11a}” for details).

During the case review, diagnoses will be reviewed, and a treatment plan will be agreed upon with the goal of minimising unnecessary diagnostic procedures, avoiding overdiagnosis, and ultimately shortening the hospital stay. Reducing the length of stay is expected to lower the risk of nosocomial complications such as hospital-acquired infections, delirium, immobility, and thromboses, all of which can prolong hospitalisation [28–30].

The 30-day readmission rate will be assessed as part of the primary outcome because it is a widely used and reliable indicator of care quality [31]. The assumption is that if reducing the length of stay through STATAMED compromises the quality of care, this would be reflected in higher readmission rates. However, Damiani et al. [19] found that short-stay wards can reduce length of stay without adversely affecting mortality or readmission rates. Furthermore, follow-up care provided by STATAMED, including support from case managers and mobile nurses, is also expected to reduce readmission rates [21]. By combining these two outcomes—length of hospital stay and 30-day hospital readmission rate—this study aims to evaluate whether a reduction in hospital stay can be achieved without compromising the quality of care for the target population.

In addition, several secondary outcomes will be analysed: utilisation of hospital emergency department, emergency outpatient care, and non-emergency outpatient care, as well as the place of discharge. These outcomes were chosen to gain a more comprehensive understanding of the entire patient pathway in relation to the treatment provided at each STATAMED ward. They are also relevant for assessing the cost-effectiveness of STATAMED.

We propose three additional hypotheses regarding the impact of STATAMED on secondary outcomes:Reduction in hospital emergency admissions and utilisation of emergency outpatient care: We hypothesise that STATAMED will reduce hospital emergency admissions and the utilisation of emergency outpatient care after initial discharge through improved coordination and the provision of follow-up care. This hypothesis is supported by findings from a systematic review by Raven et al. [32], which suggest that case management interventions can reduce emergency department visits.Non-emergency outpatient care utilisation: We expect two opposing effects on non-emergency outpatient care utilisation. Follow-up care provided by the mobile nurse may substitute for certain outpatient services, whereas the coordination of follow-up care by the case manager, including scheduling appointments with outpatient physicians, is expected to increase the utilisation of non-emergency outpatient care.Increase in discharges to home rather than nursing care facilities: We also hypothesise that patients treated at STATAMED wards will be more likely to be discharged to their homes rather than to nursing care facilities. This is attributed to improved treatment quality, which is expected to prevent overtreatment and reduce the risk of nosocomial and other complications.

A health economic evaluation will be conducted to assess the cost-effectiveness of STATAMED. We hypothesise that the enhanced hospital care provided in STATAMED wards will be more cost-effective than usual hospital care. Reducing the length of hospital stay is expected to lower costs for health insurers. Readmission rates also serve as an indicator of cost-effectiveness [31]. For example, Jencks et al. [33] estimated that unplanned readmissions of Medicare beneficiaries in 2004 cost US $17.4 billion. Reduced utilisation of emergency outpatient care is also associated with lower health care costs. Whereas increased utilisation of outpatient care may result in higher costs for outpatient treatments, it can help prevent costly readmissions to hospital.

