### Outcomes {12}

All outcomes will be measured using claims data from the participating statutory health insurers. A detailed description of the claims data is provided below (see “Plans for assessment and collection of outcomes {18a}”).

The combined primary outcome consists of the following:

(1) Length of hospital stay, which is measured in days and calculated as the difference between the admission date and discharge date. (2) A 30-day hospital readmission rate, which captures the number and length of hospital stays within 30 days after discharge

The secondary outcomes are as follows:Utilisation of hospital emergency departmentsUtilisation of emergency outpatient careUtilisation of nonemergency outpatient carePlace of discharge (discharge to patient home vs. discharge to a care facility)

Utilisation of hospital emergency departments, utilisation of emergency outpatient care, and utilisation of nonemergency outpatient care will be measured in monetary terms and by the number of services provided. These outcomes will be measured before and after the hospital stay.

A health economic evaluation will also be conducted to assess the cost-effectiveness of STATAMED.

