### Statistical methods

#### Statistical methods for primary and secondary outcomes {20a}

The two co-primary outcomes (length of hospital stay, 30-day hospital readmission rate) are treated as continuous variables. The secondary outcomes (utilisation of hospital emergency departments, emergency outpatient care, and nonemergency outpatient care, as well as place of discharge) are also continuous except for the place of discharge (home, care facility, other), which is categorial.

Because there are two co-primary outcomes without hierarchical ordering, a correction for multiple testing is required. A Bonferroni correction will be applied, resulting in a one-sided significance level of α/2 = 2.5% for each primary outcome given a global type I error rate of *α* = 5%. However, the Bonferroni method is known to be conservative. As an alternative, the Romano-Wolf procedure [43] may be used, as it more efficiently controls the family-wise error rate by accounting for the dependence structure among outcomes through resampling (see “Sample size {14}”).

When analysing stepped-wedge designs, it is important to account for temporal effects given that each cluster transitions to the intervention in a stepwise fashion. In this study, this is particularly important because the STATAMED wards will gain experience with implementing the intervention over time. Additionally, the longitudinal design of the study necessitates the consideration of calendar time because patient case mix may vary by season (e.g. winter versus summer) due to the focus of the study on general medical conditions. To account for these temporal effects, generalised linear mixed models (GLMMs) and generalised estimating equations (GEEs) will be applied [45–47]. Propensity score matching, considering age, gender, and morbidity, will be used to ensure comparability between the control and intervention groups.

To avoid bias from patients who are transferred to other hospitals during STATAMED treatment or those who meet eligibility criteria but prefer to be treated at a non-STATAMED hospital, the analysis will be conducted according to the intention-to-treat and per-protocol principles [48].

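### Readmission cannot reveal fatal harm and mortality is not an outcome, so the plan cannot show that a shorter stay leaves care quality intact

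*Protocol article*

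**What the plan says.** Objectives {7} gives readmission a specific job. It is the safeguard on shorter stays, resting on the stated assumption that "if reducing the length of stay through STATAMED compromises the quality of care, this would be reflected in higher readmission rates". By combining the two outcomes, "this study aims to evaluate whether a reduction in hospital stay can be achieved without compromising the quality of care".

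Outcomes {12} defines length of stay as days, "calculated as the difference between the admission date and discharge date". The second co-primary outcome "captures the number and length of hospital stays within 30 days after discharge". The secondary outcomes are "utilisation of hospital emergency department, emergency outpatient care, and non-emergency outpatient care, as well as the place of discharge". Place of discharge has two categories in Outcomes {12} (home or care facility). Statistical methods {20a} adds a third category, other, without defining it.

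Adverse event reporting and harms {22} provides for documenting transfers and their reasons; deaths are not mentioned. There is no data monitoring committee ({21a}). The other sub-studies named in {5d} concern patient-reported outcomes and qualitative work on implementation.

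Mortality appears only as a finding of earlier studies. Objectives {7} cites a meta-analysis for the statement that "short-stay wards can reduce length of stay without adversely affecting mortality or readmission rates". Background and rationale {6a} reports the same meta-analysis, followed by a literature review restricted to general medical conditions, which concluded that "current evidence regarding reduced mortality, serious adverse events, and rehospitalisation is insufficient to definitively assess the benefits and harms of short-stay units".

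**The concern.** A safeguard has to move in the adverse direction when the harm it guards against occurs. Readmission does so for patients who deteriorate and return to hospital. It does not do so for patients who die without returning, because they have no later stay to count. If shorter stays led to more such deaths, the readmission outcome would look slightly better.

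The question matters here because the article itself cites a review, in the trial's own type of patient, that found the mortality evidence insufficient. The population is a mixed one. An uncomplicated course is expected (PCCL 0 to 2), which points to low mortality, but the trial focuses on the elderly, and the example diagnoses include pneumonia and left ventricular failure with symptoms at rest. According to the Discussion, the evaluation will include a recommendation on adoption into routine care. A recommendation resting on shorter stays with no more readmissions, and no mortality figure, would leave the most serious form of harm unexamined.

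**Working it through.** **Step 1. What each listed outcome records when a patient dies** (definitions from Outcomes {12} and Statistical methods {20a}).

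| Event | Length of stay | Stays within 30 days after discharge | Secondary outcomes |
|---|---|---|---|
| Death in hospital | Ends at death; lower only if the stay would have lasted longer | None to count | No later utilisation; place of discharge possibly in the undefined third category |
| Death after discharge, no prior readmission | Unaffected | None to count | Utilisation stops; place of discharge unaffected |
| Death during or after a readmission | Unaffected | Readmission counted | Death itself not recorded |
| Non-fatal deterioration with return to hospital | Unaffected | Readmission counted | Emergency use may rise |

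The safeguard works in the last two rows and fails in the first two. If in-hospital deaths were instead left out of the readmission analysis, they would still not register as a worse result.

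**Step 2. Size of the effect on readmission.** The article states no mortality rate, baseline readmission rate or control length of stay, so there is no figure of its own to reproduce and all rates below are assumptions. Take 20% readmission among survivors and treat readmission as yes or no. Suppose also that no patient who dies was readmitted first. Then readmission = 0.20 × (1 − mortality).

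- Mortality 5%: 0.20 × 0.95 = 19.0%
- Mortality 7%: 0.20 × 0.93 = 18.6%, a relative fall of 0.4/19.0 = 2.1%
- Mortality 10%: 0.20 × 0.90 = 18.0%, a relative fall of 1.0/19.0 = 5.3%

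**Step 3. Sensitivity to who dies.** Step 2 supposes that those who die would have been readmitted at the average rate. Sicker patients might be readmitted more often. In general, relative change = −(d × q)/p, where d is the excess mortality, q the share of those patients who would otherwise have been readmitted, and p the control readmission rate. With assumed p of 10-20% and q of 0.5-1, each extra percentage point of mortality lowers readmission by between 0.01 × 0.5/0.20 = 2.5% and 0.01 × 1/0.10 = 10%.

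**Step 4. Could deaths create the planned effect?** Sample size {14} uses a 15% effect initially and 20% after the update. The excess mortality needed is effect × p/q.

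- For 15%: from 0.15 × 0.10/1 = 1.5 points to 0.15 × 0.20/0.5 = 6.0 points
- For 20%: from 0.20 × 0.10/1 = 2.0 points to 0.20 × 0.20/0.5 = 8.0 points
- Under the Step 2 assumptions (q = 0.20, p = 0.19), for 15%: 0.15 × 0.19/0.20 = 14.25 points

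The low ends need every excess death to be in someone who would otherwise have been readmitted. In patients with an expected uncomplicated course, deaths are unlikely to produce the whole effect.

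**Step 5. Length of stay.** Relative change in the mean = −(d × c)/L, where c is the bed-days cut off per death and L the control mean. With assumed c of 2-8 days and L of 5-7 days, one extra point of mortality lowers the mean by between 0.01 × 2/7 = 0.3% and 0.01 × 8/5 = 1.6%. This applies only to deaths that cut a stay short.

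**The case against.** The strongest defence has four parts.

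First, the article states an assumption and an aim, not a finding, and it cites a meta-analysis that found no adverse effect on mortality or readmission. That is so, and the article should not be read as claiming safety. But the aim needs an outcome able to detect the harm in question, and the review cited in Background and rationale {6a} leaves the question open for general medical patients.

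Second, readmission is not the only information. Emergency use and place of discharge are measured, transfers are documented with reasons, and a patient who returns to hospital and dies there does count as readmitted. All of this stands for non-fatal harm and narrows the problem to deaths without a prior readmission. It does not close the gap, because utilisation also stops at death, and the undefined discharge category could at most hold in-hospital deaths.

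Third, the handling of deaths in the models may sit in an analysis plan that is not shown. That is fair, and the absence of competing-event methods is not criticised here. The outcome list and the reasoning that makes readmission the quality check are protocol content and are stated in the article.

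Fourth, the numbers are small and assumed, and the illustration treats readmission as yes or no, whereas the article defines number and length of stays and treats the outcome as continuous. That also stands; the figures show direction and rough size only.

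A reader might go further and infer that death improves both co-primary outcomes, so that a positive result could be an artefact of mortality. The documents do not support this. A death lowers length of stay only when it cuts a stay short, and Step 4 shows that the planned effect is unlikely to arise this way.

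A reader might also infer that the planned 2076 participants suffice to exclude excess mortality. With an assumed 3% mortality and two independent groups of that size, the 95% half-width is 1.96 × √(2 × 0.03 × 0.97/2076) = 1.04 points. That formula ignores the ICC of 0.05 and the stepped-wedge time effects, and the article states no equal control group, so the figure cannot be relied on.

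**Conclusion.** The point holds in a limited form. The assumption in Objectives {7} is wrong for fatal harm, and no listed outcome or harms item measures death. As planned, the trial can show shorter stays and the direction of readmission, but not that care quality is preserved. If 30-day mortality rose from 5% to 7-10%, the readmission outcome would not worsen; it would improve by about 2-5% in relative terms. The fall would be larger if those who die would have been readmitted more often than average. The possible effect on length of stay is weaker and less certain.

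The conclusion about direction rests on the outcome definitions alone. The sizes rest on assumed rates that the article does not give. The concern is a harm that would stay hidden, not a spurious finding of benefit.

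**What to change.** 1. Add in-hospital and 30-day all-cause mortality as a secondary safety outcome, taken from the same insurers' claims for the intervention and control groups.
2. Report death or readmission within 30 days beside the second co-primary outcome, leaving both co-primary outcomes unchanged.
3. Reword Objectives {7} so that readmission is read as a check on care quality only together with mortality.

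Mortality should be reported descriptively, with intervals that allow for clustering and time, and without a statement that the planned size is enough to exclude harm.

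The cost is one more secondary outcome and one more data field. It is assumed that the insurers hold a date of death or a discharge reason; place of discharge already calls for discharge information from the claims. No patient contact is needed. The deliveries are planned for about June 2026 (preliminary) and January 2027 (final), so the field can be requested for the preliminary delivery and checked there for completeness. The amendment route in {25} applies: inform the ethics committee, update the registration and publish the updated protocol.
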